#### Assignment of interventions

##### Allocation

There are 66 potentially eligible CUs in the county (see above). We will select 36 CUs for inclusion in the trial. In order to ensure balance between the arms, restricted randomisation will be used. A list of the 66 CUs with their sub-county, distance from Kitale and direction from Kitale (categorised into four quadrants, North, South, East and West) will be compiled and used during randomisation. A statistician, who will not participate in recruitment, will generate a random allocation sequence. Randomisation will consider the direction, cluster size and distance from the hospital. The following restrictions will be used in the randomisation:each arm must include at least two CUs from each sub-county;each arm must include at least two CUs from each direction of North, South, East and West;the ratio between number of CUs in each arm from each direction must be in the range of 0.67–1.5;the difference in mean health centre distance from Kitale in each of the arms should not be > 4 km; andthere should not be more than one CU per link health facility.

A list of 10,000 valid permutations will be generated and checked that there are no clear deviations in randomness (e.g. pairs of health centres that occur within the same arm considerably more/less often than would be expected by chance). One of these 10,000 permutations will be computer-selected at random. A list of CUs allocated to the control group, intervention group and those not involved will be prepared.

In health facilities where there are larger catchment populations and served by more than one CU, one of the CUs will be randomly selected along with its population unit, so that the size of the clusters studied is around 5000.

#### Masking

It will not be possible to mask the participants or the health workers from the intervention to which they are allocated; however, the study statistician, hospital registration clerk and clinician assessing outcomes will be masked. The data clerk will be masked to the intervention arm because all the patients will present with paper referral. The clinician assessing secondary outcomes will not participate in patient recruitment or assessing attendance and all patients will be given similar assessment questionnaires. The statistician will not participate in patient recruitment.

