#### Interventions

A comparison of the two arms is shown in Table 2 and Fig. 1. Before the beginning of the trial, households in each of the clusters in both arms will be visited by the field team to explain the study, obtain consent (see Additional file 2) and enumerate the residents. Parents/guardians will provide consent for children. At the beginning of the trial, in both arms, there will be posters and verbal notices (churches and schools) advertising the forthcoming outreach clinic for eye checks, encouraging people with eye problems to self-report to the clinic on a specific date when the team will visit.

**Table 2 Tab2:** Comparison of the interventions in the two arms of the trial

	Intervention arm	Control arm
Consent and enumeration	Yes	Yes
Community sensitisation	Posters and announcement in churches and schools	Posters and announcement in churches and schools
Community screening	Vision assessed at household level using Peek E- acuity by field worker	No vision assessment at household level
	Screening decision using Peek Screening App	No screening
	Personalised text and weekly reminder messages for participants/carers in the relevant local language to attend appointments	No text message
Referral from community to PHC (triage centre)	Self-referring participants and referrals by CV using Peek system?	Self-referring participants
	Automatic referral through Peek system	No referrals
Provision of triage	Trained team composed of ophthalmic clinical officer, ophthalmic nurses and two field workers	Trained team composed of ophthalmic clinical officer, ophthalmic nurses and two field workers
Referral from triage centre to secondary care	Paper referral	Paper referral
	Automatic referral through Peek system and weekly reminder SMS	
Assessment of primary outcome	Same for both arms (trained field worker)	Same for both arms (trained field worker)
Assessment of referrals	Ophthalmic clinical officer	Ophthalmic clinical officer

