On the pre-advertised date, a team from KEU will be based at the CU’s dispensary. The participants referred from the household screening because of reduced vision or a specific eye problem will be reminded to attend. They will assess the presenting patients using the current standard procedure (Snellen chart visual acuity, magnifying loop, refraction and direct ophthalmoscopy when indicated). They will provide simple treatments or refer patients to KEU for further assessment as indicated. A pre-numbered paper referral letter will be given to the patient to present at KEU. The referral slip has their study number, name and triage centre, and telephone number, and indicates that assessment and treatment will be provided at no cost. It is expected that they will report to KEU within four weeks from being referred.

Immediately after referral from the PHC, an SMS will be sent to the patient and the family associate asking them to present to KEU. A weekly reminder SMS will be sent for those who have not attended their referral to KEU. An SMS with a list of patients who have not attended their referral will be sent to the CHEW responsible for the PHC.

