#### Outcomes

##### Primary outcome

The primary outcome is the number of people per 10,000 population (rate) attending triage at a local health facility (PHC) with any confirmed eye conditions (true positives) following a CV referral or by self-referral, within four weeks from the time of sensitisation. The rate will be based on baseline enumeration census for each CU. The true positives will be determined at triage by the hospital outreach team.

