#### Data collection, management and analysis

##### Data collection

In both arms, we will use electronic data capture and management using dedicated Peek software with built-in consistency checks. In both arms, this will include the enumeration data, the triage data in the health centre/dispensary and the outcome data collected in the KEU. In addition, the household screening data will also be captured electronically for the Peek arm during the study period and in the control arm following the study when the team will screen all the control clusters. Field workers will be provided with tablets for data entry. Information will be backed up regularly.

During triage assessment at the health centre/dispensary, trained field workers will verify that the participant comes from the catchment population. From each eligible participant, date of attendance, name, age, gender and own or parents’ mobile phone number, whether referred using the Peek system or self-referral, the diagnosis and treatment plan (treated or referred) will be obtained. At KEU, all referred patient will be marked as attended upon presentation and record the date of visit, diagnosis and outcome of the visit.

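### The masking claimed for the clinician assessing outcomes does not reach the triage team, which makes the confirmed-condition judgement in the primary outcome

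*Protocol article*

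**What the plan says.** All references are to the protocol article.

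- **Masking, the claim.** "the study statistician, hospital registration clerk and clinician assessing outcomes will be masked". The first half of that sentence concedes: "It will not be possible to mask the participants or the health workers from the intervention to which they are allocated".
- **Masking, the mechanisms.** For the clerk: "The data clerk will be masked to the intervention arm because all the patients will present with paper referral". The clinician assessing secondary outcomes is kept out of recruitment and of recording attendance, and the statistician is kept out of recruitment. No mechanism is given for the people who examine patients at triage.
- **Primary outcome.** "The true positives will be determined at triage by the hospital outreach team".
- **Table 2 (Interventions).** The row on assessment of the primary outcome reads "Same for both arms (trained field worker" in both columns. The provision-of-triage row lists an ophthalmic clinical officer, ophthalmic nurses and two field workers.
- **Peek CEH intervention arm.** "On the pre-advertised date, a team from KEU will be based at" the community unit's dispensary. On onward referral, the Peek system sends text messages to the patient and a family associate. Table 2 shows automatic Peek referral and text messages in the intervention arm only.
- **Data collection.** For each eligible triage attender, "whether referred using the Peek system or self-referral, the diagnosis and treatment plan (treated or referred) will be obtained".
- **Referral slip to Kitale Eye Unit (KEU).** "The referral slip has their study number, name and triage centre, and telephone number". The control-arm letter is identical.

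**The concern.** The primary outcome is more than a head count. An attender enters the numerator only if the outreach team confirms an eye condition; otherwise the same person counts towards the first secondary outcome, false-positive attendance. The line between the two is a clinical judgement, made where several features of the clinic point to the arm.

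If the assessor's expectation moves borderline attenders across that line differently by arm, the primary rate shifts although nothing has changed in who came to the clinic. The general masking claim would let the trial be reported as having masked outcome assessment for its primary outcome, and the plan does not provide that.

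**Working it through.** **1. Does any stated mechanism mask the triage assessors?**

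| Role | Outcome served | Masking mechanism stated |
|---|---|---|
| Statistician | Analysis | Not involved in recruitment |
| Registration or data clerk at KEU | KEU attendance | Paper referral in both arms |
| Clinician for secondary outcomes | Secondary | Not involved in recruitment or attendance; similar questionnaires |
| Outreach team at triage | Primary (confirmed condition) | None |

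**2. Could the arm be hidden from that team in practice?** Each clinic is held at the facility of one community unit, and allocation is by community unit, so everyone at a clinic belongs to one arm. Peek referrals exist in one arm only, and their presence is recorded for the same attender as the diagnosis. Onward referral sets off Peek messages in one arm only. The Masking section itself concedes that health workers cannot be masked. Together these make masking at triage implausible, and nothing in the article counters them.

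**3. The plan's own sample size, reproduced.** Inputs from Sample size: 1.5% v 2.0%, 5000 per cluster, intraclass correlation 0.001, 90% power, 5% significance (two-sided is my assumption).

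- Individuals per arm: [1.960·√(2·0.0175·0.9825) + 1.282·√(0.015·0.985 + 0.020·0.980)]² / 0.005² = 14,451.
- Design effect: 1 + 4999 × 0.001 = 5.999.
- Clusters per arm: 14,451 × 5.999 / 5000 = 17.3, rounded up to 18, as stated.

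The Hayes formula with its added cluster gives 18.3 to 18.4 per arm if the between-cluster coefficient of variation is derived from the intraclass correlation separately in each arm, and 21.1 to 21.2 if the control-arm value is used for both. The sample size is not at issue here; the design figures serve only as a scale.

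**4. Illustration against the target difference.** Target: 0.005 × 5000 = 25 people per cluster. Assumed Peek-arm attenders: 0.020 × 5000 = 100.

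- 5 wrongly upgraded: 5/5000 = 0.1 percentage points; 0.1/0.5 = 20% of target.
- 10 wrongly upgraded: 10/5000 = 0.2 percentage points; 0.2/0.5 = 40% of target.

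**5. Illustration under no true effect.** Assume 1.5% confirmed in both arms, 18 clusters of 5000 per arm, intraclass correlation 0.001, and a t-test with 34 degrees of freedom (critical value 2.032). Standard error of the difference: √(2 × 0.015 × 0.985 × 5.999 / (5000 × 18)) = 0.00140.

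| Over-calling in Peek arm (relative) | Extra cases per cluster | Chance of a significant result |
|---|---|---|
| 0% | 0 | 5% |
| 5% | 3.75 | 8% |
| 10% | 7.5 | 17–18% |
| 15% | 11.25 | 32–34% |
| 20% | 15 | 51–55% |

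The lower figure of each range lets the variance rise with the inflated rate; the higher keeps it at the 1.5% value.

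**6. What is immune.** If *x* attenders are moved from false to true positive, the primary count rises by *x* and the false-positive count falls by *x*, so their sum does not change. The rate of all triage attenders is therefore free of this judgement.

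**The case against.** **No sentence says that the triage team knows the arm.** This stands: it is an inference from the setting. Data are entered by field workers, and nothing shows that the examining clinician sees the referral-source item. The point therefore rests on the general claim of masking having no mechanism behind it at triage, and on the setting making such masking implausible.

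**The masked clinician may mean only the one at KEU.** That is a fair reading of the later sentence about secondary outcomes. But then the confirmed-condition judgement has no masked assessor, and the general claim still needs limiting.

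**Table 2 and the Primary outcome section can be read together.** Agreed. Field workers verify at triage that the person comes from the catchment, and the outreach team classifies the eye condition. A reader might infer a contradiction over who decides the primary outcome; the text supports only loose wording in the table.

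**A reader might infer that masking at KEU fails as well.** The slip names the triage centre, and there is at most one community unit per link facility, so the centre maps to one arm. But this reveals the arm only to someone who knows the allocation, and the article does not say that the clerk does. KEU attendance and its date are objective. Paper referral alone does not conceal the arm from staff who know the allocation, but the likely bias is small.

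**A diagnosis list may sit in the full protocol or analysis plan.** Also right, so its absence from the article is not part of this point. Nor would a list or a hidden screen remove the problem: the recorded diagnosis would still come from an unmasked clinician, and patients can disclose how they were referred.

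**Conclusion.** The point holds in a limited form. The article claims masking of the clinician assessing outcomes in general terms, but the clinical judgement inside the primary outcome is made by an outreach team for whom no masking is described and, in that setting, none is plausible. The statement should be corrected.

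The documents do not support saying that the primary result will be biased, or by how much. The 20% to 40% range and the false-positive rates rest on assumed misclassification towards the Peek arm. They also need enough attenders without an eye condition to be available for upgrading, and the article gives no such share. They show that a small shift per cluster would matter on the scale of the design; they are not estimates.

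The attendance component of the primary outcome, and the KEU attendance outcomes, are largely objective and are not materially affected.

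**What to change.** **(a) Correct the masking statement.** In Masking, say that the triage assessors who classify the primary outcome are not masked, and limit the claim to the statistician and the KEU outcome staff. In Table 2, say that field workers verify attendance and catchment, and that the outreach team classifies the eye condition.

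**(b) Add one supporting analysis.** Prespecify the cluster-level rate of all triage attenders regardless of diagnosis (true plus false positives) over the enumerated population, compared with the same unadjusted t-test, and interpret the primary result alongside it. It supports the primary analysis and does not replace it: household screening may also bring in more people without an eye condition, so a rise in all attenders alone would not show a gain in confirmed cases. Both components are already planned as cluster rates, and the Sample size section words its target as overall attendance.

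**Cost.** A less favourable masking statement, one extra analysis on data already collected, and submission of the change to the committees as an amendment. Recruitment was under way at submission; neither change alters field procedures, so clusters already completed and those still to come are handled alike.

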#### Data collection, management and analysis

##### Data collection

In both arms, we will use electronic data capture and management using dedicated Peek software with built-in consistency checks. In both arms, this will include the enumeration data, the triage data in the health centre/dispensary and the outcome data collected in the KEU. In addition, the household screening data will also be captured electronically for the Peek arm during the study period and in the control arm following the study when the team will screen all the control clusters. Field workers will be provided with tablets for data entry. Information will be backed up regularly.

During triage assessment at the health centre/dispensary, trained field workers will verify that the participant comes from the catchment population. From each eligible participant, date of attendance, name, age, gender and own or parents’ mobile phone number, whether referred using the Peek system or self-referral, the diagnosis and treatment plan (treated or referred) will be obtained. At KEU, all referred patient will be marked as attended upon presentation and record the date of visit, diagnosis and outcome of the visit.

#### Data management

Data will be entered directly onto smartphones by trained field workers and uploaded to a secure server once connected to the Internet before being exported into Stata for analysis. The database will be encrypted and password-protected. At the end of the study, the data will be archived at LSHTM.

##### Data analyses

The trial will be reported using the 2010 CONSORT guidelines, with the cluster RCT extension [51]. Analysis will be by intention to treat. Socio-demographic characteristics of participants at baseline will be tabulated by arm: age; sex; residence; and distance from hospitals (categorised distances). The distributions of these variables by intervention arm will be compared to assess whether there is imbalance at baseline in these potential confounding factors.

#### Analysis of the primary outcome

The proportion of individuals attending triage within each cluster will be calculated, by dividing the number attending triage and having a confirmed eye condition by the cluster population, which will be determined by the baseline enumeration census in both arms (true-positive attendance rate). A t-test will be performed on these cluster-level rates providing an estimate of the rate difference (with a 95% CI) between the two arms and a *P* value in order to assess the strength of evidence against the null hypothesis that the rate is equal in the two arms [52]. The two study arms should be balanced in terms of confounders due to the restricted randomisation process so the primary analysis will be unadjusted.

#### Analysis of secondary outcomes

The proportion attending triage but having no eye condition (false-positive attendance rate) will be estimated in a similar manner to the above in both arms, with a rate difference estimated, along with its 95% CI.

In order to estimate the effect of the intervention on the attendance rate of true positives at KEU the approach will be identical to the cluster-level analysis of the primary outcome. The numerator of each cluster is the number of individuals attending KEU following a referral from triage and the denominator is the cluster population. Again, a t-test will be used to assess the evidence as to whether the rate differs between arms and the analysis will again be unadjusted.

The difference in the proportion of patients referred from the PHC to the KEU who attend their referral within four weeks, by arm, will be tested using a random effects logistic regression, with attendance at KEU as the outcome, trial arm as the primary exposure and cluster as a random effect to account for within cluster correlation. Due to the fact that the characteristics of the patients referred in each arm may be different (due to the potential upstream impact of the intervention), this analysis will be adjusted for sex, age group and distance from KEU.

The impact of the intervention on time-to-attendance will be investigated, using Kaplan–Meier plots for each arm to compare attendance of referral. The hazard ratio will be estimated using Cox regression, again adjusted for sex and age group, to assess whether patients referred in the intervention arm attended their referrals sooner than those in the control arm..

We will assess possible effect modification of sex, age and distance from KEU. In the cluster-level analyses, the approach recommended by Cheung et al. [53], will be used for age and sex, where the rate in each group within each cluster will be estimated, then the difference in this rates in each group found, before finally performing a t-test on these differences by arm. In order to identify if the distance from KEU is an effect modifier, since it is a cluster-level covariate, this can be done by performing a linear regression on the cluster level rates and include distance and trial arm as exposures with an interaction term between them. For the individual-level analyses, an interaction term will be included with trial arm for each of the potential effect modifiers (age, sex, distance from KEU).

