### Trial design and overview

This trial is a single-masked, parallel-group, cluster randomised controlled trial. Thirty-six community units with their health facilities (dispensary or health centres) will be randomly selected to receive either the intervention (community screening using the Peek screening system) or the current standard of care (periodic health centre-based outreach clinics). The health workers involved in the study will be trained to ensure standardised screening. Participants who provide consent will be enrolled to the arm to which their cluster is randomised.

In the Peek arm, all households in the cluster will be visited in turn. Consenting individuals will have their visual acuity tested using the Peek visual acuity screening application on a smartphone. All participants with reduced visual acuity or reporting another eye problem will be referred to the linked PHC for assessment and management. Those requiring treatment not available from the PHC facility will be referred onwards to Kitale Eye Unit (KEU). In the control arm, communities will be notified about the periodic eye health outreach clinic that will be held in the local health centre. People attending this service will be assessed and, if necessary, referred onwards to KEU.

The participants will be followed up for eight weeks after referral from the community. The primary outcome will be the number of people per 10,000 population (rate) attending triage at a local health facility (PHC) with any confirmed eye conditions (true-positive cases determined at triage by hospital outreach team) following a referral or by self-referral within four weeks from the time of sensitisation. The secondary outcome will be the proportion of people referred from the PHC triage attending their referrals at KEU within four weeks of being referred. A participant (standard or Peek) who attends the hospital appointment within four weeks will be considered an ‘attender’ while anyone who is referred but does not attend within the same time is a ‘non-attender’.

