##### Peek CEH intervention arm

In each cluster, a small mobile team of a ‘Peek User’ (CVs trained specifically on how to use the Peek Community Screening App and who travel to multiple communities to perform their duties) and local CV will visit each household. The CV, a person from that same community, will guide the Peek User around the village. After reconfirming consent, people who are resident in the household at the time of the visit will have a vision assessment. The visual acuity of each eye will be measured separately using the Peek Acuity App [38]. This smartphone application presents a series of E-optotypes in one of four orientations, selected at random. The test algorithm prompts the following screening questions to the parents or guardian with a child (‘*Does the child have any problem with their eyes today?*’) or directly to participant themselves (‘*Do you have any discomfort or pain in your eyes today?*’ and ‘*Do you have a problem with your sight when seeing far or near objects?*’)*.* If the participant is aged ≥ 6 years, the App prompts for distant visuals acuity assessment using Peek Acuity App and assessment of near visual acuity for all people aged ≥ 40 years. Near vision will be assessed at 40 cm using the RADNER reading chart [48]. They will be referred to the PHC for subsequent assessment by the visiting time if: the visual acuity is < 6/12 in either eye; there is any self-reported eye pain or discomfort; there is difficulty seeing distant or near objects; or they are not able see N8 on near vision assessment. Household members absent during the first visit will be asked to join the examination team at the next household or next day.

Those who have reduced visual acuity on screening or report an eye problem will be referred to a health post for triage on a specific date when the KEU team visit. The system will generate several SMS text messages: (1) to the patient and family associate asking them to present to the health facility on a specific day (set to be within four weeks); (2) the CV will receive an SMS list of patients from their community that have been referred; and (3) the CHEW responsible for that CU will similarly receive the same list of referred patients. A weekly reminder SMS will be sent to the patient for them to attend their referral appointment with the last reminder being one day before the appointment.

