##### Secondary outcomes

The secondary otucomes are: (1) the number of people per 10,000 (rate) attending the triage post without any eye condition (false positives) as determined by the eye team; (2) the number of people per 10,000 population (rate) attending KEU within four weeks after being referred from PHC; (3) the proportion of participants referred from the PHC who attend the referral at KEU within four weeks of being referred from a PHC; and (4) the time taken by a participant referred from PHC to attend KEU.

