## Discussion

This trial is designed to evaluate whether the Peek Screening system in the community increases access to eye services at PHC within four weeks for patients with eye problems, as well as to assess whether the same system increases uptake of referrals of people identified with eye problems from PHC to secondary care within four weeks.

One identified limitation of the study would be the number of people who will be screened and referred but have no eye problems (false positives) and may potentially overload the health system. Through the trial, we shall analyse the potential limitations with a view of understanding and providing potential solutions in the future.

The WHO and International Agency for Prevention of Blindeness (IAPB) have set a target of eliminating avoidable blindness by 2020 through early identification and treatement. This study aims to evaluate a system to reduce the prevalence of people with VI through early identification and referral from the community for those with ophthalmic ailments. The system will potentially increase access and uptake of eye services through screening and referral by CVs, for those with eye problems. Through the system, we shall be able to track the process of screening and referral of patients with a view of identifying gaps in the health system and advise policy makers on potential solutions. The results will therefore be relevant and contribute towards realising this goal.

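### Referral uptake and time to attendance are compared within a group the intervention itself changes, and the adjustment omits the diagnosis recorded at triage

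*Protocol article*

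**What the plan says.** The protocol article's list of secondary outcomes includes "the proportion of participants referred from the PHC who attend the referral at KEU within four weeks of being referred from a PHC" (outcome 3) and the time a referred patient takes to attend (outcome 4). Trial design and overview gives the former prominence: "The secondary outcome will be the proportion of people referred from the PHC triage attending their referrals at KEU". The Discussion states the aim in similar terms, to "assess whether the same system increases uptake of referrals of people identified with eye problems from PHC to secondary care within four weeks".

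Analysis of secondary outcomes sees a difficulty with outcome 3: "the characteristics of the patients referred in each arm may be different (due to the potential upstream impact of the intervention"). Its response for the random-effects logistic model is that "this analysis will be adjusted for sex, age group and distance from KEU". The Cox model for outcome 4 is "again adjusted for sex and age group", without distance.

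The same section also plans a cluster-level analysis of KEU attendance with the enumerated cluster population as denominator (outcome 2).

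**The concern.** Randomisation makes the enumerated populations comparable. It does not make the patients referred from triage comparable when the intervention decides, in part, who gets to triage. If household screening brings in people whose problems are milder, or of another kind, than those of people who come unprompted, their readiness to travel on to KEU may differ for reasons unrelated to anything done after referral.

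An adjusted odds ratio or hazard ratio could then be read as an effect of the Peek system on uptake after referral when it reflects case mix, or a real effect could be masked. The adjustment shows that the protocol wants a like-for-like comparison, but the chosen covariates are poorly matched to that purpose.

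**Working it through.** **1. The plan's own figure.** None is stated for referral uptake. The 36 clusters concern triage attendance, and they reproduce. For 1.5% vs 2.0%, 90% power and 5% significance (two-sided assumed), about 14,451 people per arm are needed. The design effect is 1 + 4,999 × 0.001 = 5.999, and 14,451 × 5.999 / 5,000 = 17.3, hence 18 clusters per arm. The point here is therefore structural and does not correct an arithmetic error.

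**2. Routes into the referred group.**
- Control (Standard of care arm; Table 2): self-referral after posters and announcements, with no household screening.
- Peek (Peek CEH intervention arm; Table 2): self-referral as well, plus household referral on criteria that include "the visual acuity is < 6/12 in either eye; there is any self-reported eye pain or discomfort", with SMS reminders.

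Raising triage attendance is the primary hypothesis. If the design effect occurs, the Peek excess is (2.0 − 1.5) / 2.0 = 25% of Peek attenders. The better the system works, the less alike the two referred groups may be.

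**3. What the covariates can do.** The analysis section itself treats distance as a cluster-level variable, and the allocation already limits the between-arm difference in mean distance to 4 km. Distance cannot describe which patients within a cluster were drawn to triage. That leaves age group and sex to stand in for the type of problem.

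The Data collection section lists the triage fields. Diagnosis is among them in both arms but enters neither model. Referral route is also listed, but it takes a single value in the control arm, so adjusting for it cannot restore comparability. Acuity belongs to the triage examination ("Snellen chart visual acuity, magnifying loop, refraction and direct ophthalmoscopy when indicated"), which is identical in both arms, but it is not named among the recorded fields.

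**4. Illustration only.** The document gives no attendance or severity figures, so all of these are assumed. KEU attendance is 60% for marked and 30% for mild disease, and 80% of control referrals are marked. Control attendance is 0.80 × 60% + 0.20 × 30% = 54%.

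| Peek referrals marked | Peek attendance, no true effect | Odds ratio | Crude difference if the true effect is +10 points |
|---|---|---|---|
| 80% | 54.0% | 1.00 | +10.0 |
| 65% | 49.5% | 0.84 | +5.5 |
| 50% | 45.0% | 0.70 | +1.0 |

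With the selection reversed (control 50% marked, Peek 80%) and no true effect, attendance is 45% vs 54% and the odds ratio is 1.44.

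A simulation (500 replicates, 36 clusters, 30 control and 40 Peek referrals per cluster, 80% of control referrals marked) adjusted for age and sex only:
- No true effect: odds ratio 0.84 (24% rejections) at 65% marked in Peek and 0.70 (70% rejections) at 50%.
- True odds ratio 1.5: estimated as 1.20 at 65% and 1.00 at 50%.
- With the severity covariate added: 1.00 under no effect and 1.48 to 1.49 under 1.5.

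The last result is by construction, since severity was the only source of selection. The simulation used cluster-robust logistic regression, not the planned random-effects model. Its null rejection was 7 to 9% even with equal case mix, so the other rejection rates should be read against that level.

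**5. Can outcome 2 replace outcomes 3 and 4?** Assume no reminder effect, the same share r of triage attenders referred in each arm, 60% KEU attendance among self-presenters, and 40% among the extra 25% found at home. Peek attendance among those referred is 0.75 × 60% + 0.25 × 40% = 55%. The population rates are:
- Control: 1.5% × r × 0.60 = 0.90% × r.
- Peek: 2.0% × r × 0.55 = 1.10% × r.

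The ratio is 1.10 / 0.90 = 1.22. At 50% attendance among home-detected cases, the Peek rate is 2.0% × r × 0.575 = 1.15% × r and the ratio is 1.28. The population rate rises by 22 to 28% through detection alone.

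**The case against.** The protocol discloses the selection, adjusts for it in part, and lists the population-based KEU rate ahead of the conditional proportion. It is also testing a whole system. The Abstract's hypothesis contrasts people identified by Peek with people identified by current methods, so a lower uptake among Peek referrals may partly be a true description of how the system performs. Home-detected patients in this denominator have already complied with one referral by attending triage, so a large deficit in their onward attendance is not evident. All of this stands. It limits the point to covariate choice and labelling, but it does not make the adjusted ratios randomised comparisons.

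Three stronger readings are tempting and are not supported:
- A reader might infer that outcome 2 should carry the conclusion on uptake. It cannot, because it combines detection with uptake (step 5).
- A reader might infer that recorded acuity is being ignored. The article shows that acuity is measured, not that it is captured in the triage record.
- A reader might take 55% vs 60% as an expected bias of −5 points. Those attendance rates are assumptions, and the 25% share refers to triage attenders, not to patients referred onward.

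**Conclusion.** The point holds as a matter of structure. Outcomes 3 and 4 compare arms within a group that the intervention alters. The protocol recognises this for outcome 3, yet its adjustment leaves out the one clinical descriptor that it says is recorded at triage in both arms. Case mix could hide or mimic an effect on uptake. The document fixes neither the direction nor the size; the odds ratios of 0.70 and 1.44 show only that either direction is possible under assumed inputs.

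Outcome 2 supports a randomised statement about the whole system's effect on KEU attendance, and no more than that. A reader might also infer that the trial's main result is compromised. It is not: the primary outcome uses the enumerated population as its denominator. This is an inexpensive improvement to two secondary analyses.

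**What to change.** - Add diagnosis group at triage to both the logistic and the Cox model, and presenting acuity as well if it is confirmed to be captured in the triage record.
- State that the conditional proportion and the hazard ratio are non-randomised comparisons open to selection, and report them beside outcome 2.
- Present outcome 2 as the effect of the whole system on KEU attendance, combining detection and uptake, and not as the effect on uptake after referral.

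The cost is a change of analysis wording and a few more model parameters, with no new visits or sample. Selection on willingness to seek care would remain, since neither diagnosis nor acuity measures it; that is why the labelling is needed as well as the covariates.
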